**2. Observation and treatment of adverse events**

Observation and record: Investigators should carefully observe any adverse events occurred in the subjects during the clinical study, require the subjects accurately reflect the changes in condition after medication, and avoid the inductive questions. When observing the therapeutic effect, it should also pay attention to observe unexpected toxicity and side effects (including symptoms, signs and laboratory tests). Adverse events should be recorded in the CRF no matter whether or not associated with the investigational drug, including the occurrence time of adverse reactions, symptoms, signs, degree, duration, laboratory indexes, processing methods, course, results, and follow-up time, and status on combined therapy should be recorded in details in order to analyze the correlation between adverse events and the investigational drug, and the record should be signed and dated.

Medical treatment of subjects: When adverse reactions are found, investigators can take the necessary treatment measures to according to the disease condition, e.g., to adjust the dose, temporarily discontinue the medication, etc., and decide whether to terminate the trial. When serious adverse events occur, units responsible for carrying out the study should take the necessary treatment measures immediately to protect the safety of subjects.

**3. Classification of adverse reactions**

**Mild:** tolerable to the subjects, not affecting the treatment, requiring no special treatment, not affecting the health of subjects.

**Moderate:** unbearable to the subjects, requiring drug withdrawal or special treatment, directly affecting the health of subjects.

**Severe:** life-threatening to the subjects, leading to death or disability, requiring immediate withdrawal or emergency treatment.

**4. Evaluation of correlation between adverse events and the investigational drug**

In accordance with the *Regulation on Reporting and Monitoring of Adverse Drug Reactions*” released by State Food and Drug Administration of China on March 4, 2004, the investigators should carry out a comprehensive analysis according to the specific status on the adverse events occurred in the subject, and the subject’s past medical history, concomitant diseases as well as concomitant medication to determine the relationship between adverse events and the drug. Adverse events determined as definitely relevant, probably relevant, and possibly relevant are considered as adverse drug reactions for statistics of the incidence of adverse reactions.

4.1 Definitely relevant to the investigational drug

There is evidence of using the investigational drug; the occurrence of adverse events and the use of the investigational drug are in chronological order that is reliable; using the investigational drug to explain the cause of the adverse events is more reasonable than using other reasons; the withdrawal reaction is positive; the repeated medication tests are positive; the pattern of adverse events is consistent with the previous understanding of this drug or this kind of drugs.

4.2 Probably relevant to the investigational drug

There is evidence for using the investigational drug; the occurrence of adverse events and the use of the investigational drug are in chronological order that is reliable; using the investigational drug to explain the cause of the adverse events is more reasonable than using other reasons; the withdrawal reaction is positive.

4.3 Possibly relevant to the investigational drug

There is evidence for using the investigational drug; the occurrence of adverse events and the use of the investigational drug are in chronological order that is reliable; the adverse events may be caused by the investigational drug or may be caused by other reasons, the withdrawal reaction is positive.

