**Classification of hypoglycemic reactions:**

| **Classification** | **Clinical manifestation** | **Treatment** |
| --- | --- | --- |
| Hypoglycemia | Tachycardia, palpitations, trembling, sweating, hunger, dizziness, blurred vision, impaired concentration, behavior disorders, etc. Patients do not need assistance from others, and can take the initiative to seek treatment. Or blood glucose <63 mg/dL (3.5 mmol/L) [IFCC plasma :< 68 mg/dL (3.8 mmol/L)], even if not accompanied by symptoms, signs or not requiring treatment. | Rapid remission after eating carbohydrates |
| Severe hypoglycemia | Hypoglycemia leads to manifestations such as coma, seizures or nervous system damage, and the patient cannot take the initiative to require treatment or seek help. Accompanied by blood glucose < 50 mg/dL (2.8 mmol/L) [IFCC plasma: < 55 mg/dL (3.0 mmol/L)] | Requiring intravenous bolus injection of glucose or glucagon injection for emergency treatment |
| Nocturnal hypoglycemia | Nocturnal hypoglycemia refers to the event that occurs before the 1st meal (e.g. breakfast) after wake up from falling sleep, presenting with clinical manifestations and blood glucose values of hypoglycemia or severe hypoglycemia | Mild patients should take food, while severe patients need intravenous injection of glucose |

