4.4 Possibly irrelevant to the investigational drug

There is evidence for using the investigational drug; the adverse events may be caused by other reasons, the withdrawal reaction is negative or equivocal; the repeated medication tests are negative or equivocal..

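### All three causality classes counted as adverse drug reactions require a positive withdrawal reaction, so reactions where the drug is continued unchanged, and fatal or irreversible ones, drop out of the incidence

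*Protocol*

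**What the plan says.** Section X.4 asks the investigator to weigh each adverse event and place it in one of six classes, 4.1 to 4.6. Events judged "definitely relevant, probably relevant, and possibly relevant are considered as adverse drug reactions for statistics of the incidence of adverse reactions". Classes 4.4 to 4.6 are not counted.

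The withdrawal condition in each counted class reads:

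- 4.1, definite: "the withdrawal reaction is positive; the repeated medication tests are positive"
- 4.2, probable: the drug explanation "is more reasonable than using other reasons; the withdrawal reaction is positive"
- 4.3, possible: "the adverse events may be caused by the investigational drug or may be caused by other reasons, the withdrawal reaction is positive"

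The next class down, 4.4, is for events where "the withdrawal reaction is negative or equivocal; the repeated medication tests are negative or equivocal".

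Three other parts of section X bear on this. Item 1.3 defines an adverse drug reaction by its causal link to the drug and sets no withdrawal condition. Item 2 lets the investigator adjust the dose or stop the drug temporarily, and requires neither. Item 3 grades a mild reaction as "tolerable to the subjects, not affecting the treatment, requiring no special treatment", and its severe grade includes reactions that end in death or disability.

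**The concern.** A causality scale normally becomes less demanding as the label becomes weaker. Here rechallenge is dropped after 4.1 and the preference for the drug explanation is dropped after 4.2, but the positive withdrawal result stays throughout. The lowest counted class therefore depends on information that exists only if the drug was stopped, or perhaps reduced, and the event then improved.

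Two groups lack that information by their nature: reactions tolerated while treatment goes on, and reactions that kill or leave permanent harm. Item 3 of the same section creates a grade for each of them as an adverse reaction, and the scale then gives neither a way into the reaction count.

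At stake are the reported adverse drug reaction incidence and the relatedness label on individual events. The label has a practical use: section X.5 ties the sponsor's payment of treatment costs and compensation to serious events determined to be related to the drug, and the document offers no other scale for that determination. Investigators assign the class at the site, so a later SAP cannot put back events already placed outside the counted classes.

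**Working it through.** The protocol gives no figure to reproduce, so the check is one of logic. Take an event with documented drug use, a reliable time order and no other significant cause. The drug is continued unchanged and the event passes or persists. Test it against each class.

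| Class | Counted? | Decisive condition | Met? |
|---|---|---|---|
| 4.1 definite | yes | positive withdrawal and positive repeat exposure | no, neither was done |
| 4.2 probable | yes | positive withdrawal | no |
| 4.3 possible | yes | positive withdrawal | no |
| 4.4 possibly not related | no | withdrawal and repeat exposure each negative or equivocal | no if read literally; yes if not done is read as equivocal |
| 4.5 to be evaluated | no | unreliable time order | no |
| 4.6 cannot be evaluated | no | drug not used, or another significant cause | no |

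The event meets 0 of the 3 counted classes. Read literally it fits none of the six. Read loosely it goes to 4.4, which is not counted. Both readings keep it out of the incidence.

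Repeat the test for a fatal or irreversible event. The event cannot improve on withdrawal, so 4.1, 4.2 and 4.3 fail again. If the drug was stopped and nothing improved, the result could be recorded as negative, which points towards 4.4 although it says nothing about cause.

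Now set the scale beside the rest of section X:

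- Item 1.3 needs a causal relationship only. Section X.4 in effect adds a second requirement, improvement on withdrawal.
- Item 3 defines mild adverse reactions as leaving treatment unaffected, so there is normally no withdrawal to assess. The mild grade and the counted classes can hardly overlap.
- Item 3 includes death and disability in its severe grade. Such reactions cannot show a positive withdrawal result.

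On size, let f be the share of patients with a true reaction who have at least one reaction with a positive withdrawal result. If nothing else is miscounted, counted incidence = f × true incidence, and the relative understatement is 1 − f. The documents give neither f nor any reaction rate, so the direction is known and the amount is not.

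**The case against.** **The wording may be looser in practice.** The protocol does not define a withdrawal reaction. Improvement after a dose reduction or temporary stop, both allowed by section X.2, could be read as positive. Section X.4 also asks for a comprehensive assessment under a national regulation that is not reproduced. This stands in part: it narrows the affected group to events with the drug continued unchanged and to fatal or irreversible events. It gives those events no written route into a counted class.

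**The loss falls mainly on mild reactions.** Moderate and severe reactions are graded partly by the need for withdrawal, so many will have a result. This is fair, but those two grades also admit reactions handled by special or emergency treatment without withdrawal, as well as fatal and disabling outcomes.

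A reader might also infer four stronger things, which the documents do not support.

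- *The comparison of safety between arms is biased towards similarity.* Section XII.6 compares adverse events between arms with no causality filter; relationship to the drug is only a listing variable. Section XII specifies no test of the reaction incidence. The protocol makes no safety non-inferiority claim, and its anticipated results expect similarity only in glycemic control.
- *Hypoglycemia is under-counted.* An ordinary episode is described as resolving by "Rapid remission after eating carbohydrates", so withdrawal is rarely in question. But hypoglycemia is a secondary endpoint (section III.2.1), defined by symptoms or glucose level without a causality condition (section X.1.4), and analysed separately (sections XII.1 and XII.8).
- *Serious or fatal events are lost.* Section X.2 records every event whatever its relation to the drug, and section X.5 reports every serious event within 24 hours on the same basis. Only the relatedness label is affected.
- *The understatement can be put at, say, 50% to 90%.* That range is only 1 − f for assumed values of f from 0.5 down to 0.1. With assumed true rates of 20% and 15% and f = 0.2 in both arms, the counted rates are 0.2 × 20% = 4% and 0.2 × 15% = 3%. The difference falls from 5 points to 1, while the relative risk stays at 20/15 = 4/3 = 1.33. None of these inputs comes from the trial.

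**Conclusion.** The point holds as a defect in a stated rule. Followed as written, section X.4 produces an adverse drug reaction incidence that leaves out events which items 1.3 and 3 of the same section treat as adverse reactions. The reported incidence is too low whenever a true reaction occurs with the drug continued unchanged or has a fatal or irreversible outcome. The documents do not allow the size to be computed.

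The reach is limited to the reaction incidence and to relatedness judgements, including those behind compensation in section X.5. The all-cause comparison, serious event reporting and the hypoglycemia analyses do not depend on the scale. The conclusion assumes that investigators apply the listed conditions as conditions. If they treat them as loose guidance, the loss is smaller, but the classification then varies between sites in a way the protocol does not control.

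**What to change.** Make two wording changes in section X.4:

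- **4.3:** change the condition so that the withdrawal reaction is positive, not done or not assessable. Not assessable should be understood to cover fatal and irreversible events.
- **4.4:** state that a negative or equivocal result refers to a withdrawal that was carried out, so that not done does not place an event in this class.

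Classes 4.1 and 4.2 can stay as they are. Both 4.2 and 4.3 are counted, so once 4.3 is widened, relaxing 4.2 would only move events between counted classes and leave the incidence unchanged. No added sentence on hypoglycemia is needed.

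The cost is two lines in the protocol and matching guidance for completing the CRF. Reported reaction rates become higher. The counted group also becomes less specific, because an event with reliable timing that might have another explanation will now count as possibly related when the drug was not withdrawn. The change concerns classification only and leaves patient management alone.

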4.4 Possibly irrelevant to the investigational drug

There is evidence for using the investigational drug; the adverse events may be caused by other reasons, the withdrawal reaction is negative or equivocal; the repeated medication tests are negative or equivocal..

4.5 To be evaluated

The emergence of adverse events and use of the investigational drug are in a chronological order that is unreliable;

4.6 Unable to be evaluated

Patients did not use the investigational drug; or there are other significant reasons that can lead to adverse events.

**5. Serious adverse events and reporting**

For any serious adverse events occurred during the trial, regardless of whether related to the investigational drug or not, the investigators should give timely rescue and treatment, and report to the Ethics Committee of the units responsible for the clinical trial and the sponsor within 24 hours, the sponsor and the investigators should promptly research the serious adverse events occurred, and take the necessary measures to ensure the safety and interests of the subjects, and report to the drug administrative department and health authority in a timely manner, simultaneously report to other researchers of clinical trials involving in the same drug. For serious adverse events that are determined as related to the investigational drug, the sponsor should bear the costs of rescue and treatment of patients and provide the corresponding economic compensation.

Investigators must fill out the “Serious Adverse Event Report Form”, and should record in the original data that when and in what way the serious adverse events occurred, whom they are reported. The sponsor should ensure the reporting procedures that meet the requirements of all laws and regulations.

| Unit | Contact | Tel |
| --- | --- | --- |
| Peking University People's Hospital | [name] | [name] |
| Guangzhou Zhongyi Pharmaceutical Co., Ltd. | [name] | [name] |
| Guangzhou Boji Clinical Research Center of New Drugs | [name] | [name]、[name] |

**6. Follow-up**

All adverse events should be followed up till they turn normal or basically normal, so as to ensure the safety of the subjects. According to the severity of adverse reactions, it can select hospitalization, outpatient visit, home visit, telephone, communication and other forms as the way of follow-up.

## XI. Data Management

1. Requirements for filling in data by the investigators

The investigators should ensure that the data is true, accurate, complete, timely and legally recorded in the case report form.

1.1 For patients who enter the trial after completion of the informed consent and determined as eligible through screening, it should carefully and detailedly record all the information that have been observed in the case report forms, without blank entry or omissions.

1.2 It should verify that all the data in the case report forms are completely consistent with the data in the original medical records.

1.3 If it is to make any correction on the case report form that is considered as the original data, it can only use scribing and sidenotes while signed and dated by the investigator.

1.4 The original laboratory test sheet (or a copy of the original laboratory test sheet) should be pasted to the corresponding place in the original medical records.

1.5 Data that is significantly higher or lower, or out of the range that can be accepted in clinical practice, should be verified or reviewed, and necessary explanation should be made by the investigators.

2. Requirements for data auditing by auditors

2.1 Auditors should regularly visit each test center during the trial check the informed consent, screening and inclusion of subjects.

2.2 Ensure that all case report forms are correctly completed and consistent with the original data.

2.3 All errors or omissions have been corrected or noted, signed and dated by the investigators.

2.4 Confirm and record the dose modification, alteration of treatment, combined medication, intercurrent diseases.

2.5 Verify that all the withdrawal and loss of visit of subjects are stated in Case Report Form.

2.6 Verify that all adverse events have been documented, serious adverse events have been reported within the specified time and documented.

2.7 Verify whether the study drugs supplied, stored, distributed, and recovered in accordance with relevant provisions, and make the corresponding records.

3. Database creation and data entry

3.1 Database creation: establish a database system specifically for the trial according to the items in the Case Report Form.

3.2 Data entry: data synchronization entry is made by the data administrator, using two-time entry method.

3.3 Data verification: check each item of the data; for inconsistent values reported, check the original questionnaire one by one, and make corrections.

3.4 If the data administrators have questions in the process of data entry, they may fill out the “data question listing” and return it to the auditors, the investigators will answer the questions in written and sign, and return it to the data administrator. “Data question listing “must be properly preserved.

## XII. Statistical analysis

**1. General considerations**

The efficacy analysis will be based on intention to treat (ITT) population, with supportive analysis with per protocol set (PPS). The PPS includes all randomized patients who have received treatment with study drugs for 48 weeks without violation to inclusion/exclusion criteria or criteria for termination of the study. The ITT population includes all randomized patients receiving at least one dose of study drugs. The safety analysis will be based on ITT population.

For efficacy analyses, changes in the primary and secondary study parameters at 48 week from baseline will be measured, and the inference on the possible non-inferiority will be based on the upper limit of the 95% confidence intervals of the difference in mean changes at 48 week. The incidence and average rate of hypoglycemia will be analyzed using appropriate statistical methods.

A separate statistical analysis plan will be developed in due course detailing all aspects of data analysis. Appropriate exploratory analyses will be conducted, as deemed appropriate.

**2. Treatment of patients**

It will list the main reason for termination of the study by the patients, and will list the incidence and percentage of all patients by treatment groups and visit time. Fisher’s exact test will be used for comparison between treatment groups.

**3. Patients’ features**

Categorical variables (such as sex and ethnicity) will be summarized using the frequency and percentage. Continuous variables (such as BMI and baseline HbA1c) will be summarized using mean, standard deviation, and limit values (minimum and maximum).

**4. Combined medication**

It will list the combined medication on all randomized patients, which will be summarized by treatment groups.

**5. Treatment compliance**

In each visit, the investigators will evaluate patients’ compliance based on glycemic blood control of patients, compliance with visit time, completion of patient diaries, and any indicators considered as necessary by the investigators. It will not collect specific research data for the analysis of treatment compliance.

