**2. Trial goals**

2.1 To discover biomarkers related to the clinical efficacy of Xiaoke Pills with glibenclamide as a reference.

2.2 To discover biomarkers related to the main side effect, i.e., hypoglycemia and study pathophysiological and clinical features of susceptibility to hypoglycemia.

2.3 To discover the unique efficacy of Xiaoke Pills compared with sulfonylureas, as well as the biomarkers associated with the unique efficacy of Xiaoke Pills.

2.4 To discover biomarkers, pathophysiological and clinical features associated with secondary failure of sulfonylureas. To investigate if Xiaoke Pills can reduce the risk of secondary failure of sulfonylureas as compared with glibenclamide.

2.5 Apply the TCM evaluation indexes to evaluate the efficacy and safety of Xiaoke Pills and glibenclamide tablets from the view of treatment of type 2 diabetes belonging to the syndrome of dual deficiency of qi and yin, and to found the biomarkers associated with above evaluation indexes.

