## IV. The overall design of the trial

**1. Sample size**

The sample size of the trial is designed and estimated according to non-inferiority test. The assumption of non-inferiority test is that the Xiaoke pill is not inferior to glibenclamide in terms of reducing HbA1c. Xiaoke Pill was regarded as non-inferior to treatment with Glibenclamide only if, after 48 weeks of treatment, the upper limit of the two-sided 95% CI for the difference in mean HbA1c change was less than 0.4%. A sample size of 400 patients was estimated to provide more than 90% power to test the hypothesis that Xiaoke Pill treatment was non-inferior to treatment with Glibenclamide in each of the study groups, assuming a 20% early discontinuation rate, and an expected inter-patient SD of 1.1%. The sample size estimation is based on being able to provide sufficient amount of information.

According to statistical results of sample size, in order to better guide the clinical application of Xiaoke Pills to improve the effectiveness of medication, this study is plan to enroll 400 non-obese patients with type 2 diabetes who have not received any antidiabetic agents before and have unsatisfactory glycemic control on diet and exercise and 400 patients with type 2 diabetes who have unsatisfactory glycemic control after treatment with metformin alone for over 3 months. 800 patients will be randomly assigned to the treatment groups and control group.

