**5. Termination (withdrawal)**

In the following situations, the study will be terminated for the patients, but the patients will be included in the FAS statistics:

5.1 If the female patient gets pregnant (violation to the protocol).

5.2 If the patient has not used the study drugs (including metformin) in accordance with therequirements of the protocol for more than 7 consecutive days.

5.3 If the patient has used insulin for more than 7 days, or month than 7 days within 1 month.

5.4 If the patient has used combined therapy with the drugs that should be excluded for more than 7 days.

5.5 If the patient’s (finger whole blood) fasting blood glucose has been greater than 234 mg/dL (13 mmol/L) for 3 consecutive times (lack of efficacy).

5.6 Serious adverse events occur.

5.7 If the patient has recurrent hypoglycemia (more than 2 episodes of hypoglycemia per week in 4 consecutive weeks), especially severe hypoglycemia (more than 2 episodes of severe hypoglycemia within 30 days), the investigator must consider terminating the trial for the patient.

If the investigators determine the patients should withdraw from the trail because of serious adverse events or significantly increased clinical laboratory parameters, appropriate measures should be taken immediately and the principal of the study should be notified.

The investigators terminate the trial or terminate the patients to participate in the trial for any reason; those patients under early termination will continue to carry out the visit procedures for early termination as specified in the protocol procedures.

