**6. Drug inventory and preservation**

The number, shipment, delivery, transition, storage, distribution, recycling, and destruction of study drugs should all be recorded. The records are preserved as the clinical trial documents.

After arrived at each clinical trial center, all study drugs should be submitted to designated personnel and managed at the designated place that meets the requirements of drug storage, and released by designated personnel do not participate in the clinical trial.

Trail managers should regularly check the quality of the drugs.

It only allows the investigators to use the study drugs, and the investigators must ensure that all drugs are only used in subjects enrolled in the clinical trial, and are used strictly in accordance with the clinical trial protocol.

The investigators should recover the remaining drugs at each return visit. After the clinical trial is completed, designated personnel from the sponsor should recover all the remaining study drugs in time.

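### Compliance is not measured independently of glucose, although a termination rule and the per-protocol set depend on whether drug was taken

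*Protocol*

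**What the plan says.** Protocol section XII.5 (Treatment compliance) has investigators evaluate compliance at each visit from glycaemic control, adherence to visit times, diary completion and any other indicator they think necessary. It then closes the matter: "It will not collect specific research data for the analysis of treatment compliance".

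Other parts of the protocol rely on, or generate, information about drug use:

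- Section V.5, item 5.2, lists as a reason for ending participation: "If the patient has not used the study drugs (including metformin"), as the protocol requires, for more than 7 consecutive days.
- Section XII.1 makes the ITT population primary. The supportive per-protocol set is limited to patients treated for 48 weeks who did not breach the entry or termination criteria.
- Section VI.6 says: "The investigators should recover the remaining drugs at each return visit". It also says: "The number, shipment, delivery, transition, storage, distribution, recycling, and destruction of study drugs should all be recorded". The trial procedures table ticks recovery of investigational drug at every visit from week 4 to week 48, and section XI, item 2.7, has auditors verify recovery.
- Section VI.2 packs each visit cycle at the highest dose that might be needed.
- Section II.2 seeks biomarkers of efficacy (goal 2.1) and, in goal 2.4: "To discover biomarkers, pathophysiological and clinical features associated with secondary failure of sulfonylureas".

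**The concern.** There are two problems.

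The first is what goes unmeasured. In a non-inferiority comparison, drug left untaken in both arms tends to pull a real difference towards zero, which favours the claim. Item 5.2 and the per-protocol set are meant to deal with continuous interruptions of more than 7 days. Shorter gaps and habitual under-dosing fall through, and nothing in the planned data would show how common they are or whether they differ by arm.

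The second is the substitute measure. Judging compliance partly from glycaemic control uses something close to the endpoint. A poor glucose response may mean that the drug was not taken or that it did not work, and this judgement cannot tell the two apart. If item 5.2 is applied on that basis, per-protocol membership is partly selected on outcome. The same ambiguity enters the response and failure phenotypes for goals 2.1 and 2.4, where it can run either way: a non-taker may look like a non-responder, or a true non-responder may be recorded as non-compliant.

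**Working it through.** **1. The plan's own figure.** Section IV.1 sets non-inferiority as "the upper limit of the two-sided 95% CI for the difference in mean HbA1c change was less than 0.4" per cent. It says "A sample size of 400 patients was estimated to provide more than 90% power", "assuming a 20% early discontinuation rate, and an expected inter-patient SD of 1.1" per cent. Allocation is 1:1, and 200:200 within each of the two patient groups. With one-sided alpha 0.025, 90% power and a true difference of 0:

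- n per arm = 2 × 1.1² × (1.960 + 1.282)² / 0.4² = 159 after rounding up.
- Inflated for 20% discontinuation: 159 / 0.80 = 199 per arm, or 398 in total, against 400 stated.
- With 200 × 0.80 = 160 evaluable per arm, SE = 1.1 × √(2/160) = 0.123 and power = Φ(0.4/0.123 − 1.96) = 90.2%.

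The stated size reproduces as a per-group figure. No number in the plan is disputed.

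**2. Illustration of dilution.** The protocol gives no non-adherence rate, so 0% to 30% is assumed, equal in both arms. Suppose a fraction f of drug is untaken and the between-arm difference d shrinks in proportion, to (1 − f)d. Then

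P(declare non-inferior) = Φ((0.4 − (1 − f)d)/SE − 1.96).

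With d = 0.4, so that every declaration is an error:

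| f | Difference seen | 160 per arm (SE 0.123) | 200 per arm (SE 0.110) |
|---|---|---|---|
| 0% | 0.40 | 2.5% | 2.5% |
| 10% | 0.36 | 5.1% | 5.5% |
| 20% | 0.32 | 9.5% | 10.9% |
| 30% | 0.28 | about 16% | 19.2% |

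For example, at f = 20% and 160 per arm: (0.4 − 0.32)/0.123 − 1.96 = −1.31, and Φ(−1.31) = 9.5%. Put another way, at f = 20% a true on-drug difference of 0.5% appears as 0.8 × 0.5 = 0.40%.

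**3. What the existing records can and cannot supply.** Leftover investigational drug comes back at each visit, so the raw material for a count exists. A bare count of returns is not enough, because kits are filled for the maximal dose. Over a 28-day cycle, 30 pills a day is 840 pills. A fully compliant patient on the initial 5 pills a day uses 28 × 5 = 140 and returns 700 (assuming no overage). Returns must be set against the dose prescribed for that interval. Section VI.6 requires recovery and a drug inventory, but does not expressly ask for a count per patient and visit. For metformin, the procedures table ticks release only at run-in and has no recovery line, although item 5.2 covers it.

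**The case against.** The strongest reply is that the protocol does assess compliance. Investigators evaluate it at every visit, may use any indicator they find useful (returned drug included), and have diaries. Auditors check dose changes and drug recovery, and the last medication time is recorded for lost cases. What is ruled out is only specific research data for analysis, and a separate statistical analysis plan is promised. This stands in part. A reader might infer that non-adherence could never be seen, or that item 5.2 has no information behind it. The documents do not support either, because site records might allow later reconstruction. What is missing is a stated measure and method. A later analysis plan cannot supply data that the CRF did not capture.

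A reader might also infer that patients who skip the drug will be classed as non-responders or sulfonylurea failures. Dose adjustment is driven by fasting glucose, so such a patient can climb to the top dose. But the protocol does not define secondary failure, and the misclassification can go in the other direction. The documents show an ambiguity, not a direction of bias.

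The dilution figures are also open to challenge. The non-adherence rates are assumed, the true difference is placed exactly at the margin, and titration is ignored. Titration would escalate low takers and partly make up for missed drug until the dose cap. All of this is right, so the figures show sensitivity and do not predict the trial's error rate.

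Finally, an adherence-based analysis conditions on behaviour after randomization and does not restore a protected comparison. That also stands, and limits how such an analysis may be used.

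**Conclusion.** The point holds as an internal conflict with a practical consequence. The protocol declines to collect compliance data for analysis, yet has a termination rule and a per-protocol set that turn on drug use. The assessment that it does describe leans on a measure close to the endpoint. Partial and intermittent non-adherence is unmeasured, and per-protocol membership may be decided on an outcome-related judgement.

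No stated figure is wrong and the sample size reproduces. The size of the effect on the non-inferiority conclusion is unknown. Under the assumptions shown, one-sided error at the margin would move from 2.5% to between about 5% and 16% with 160 evaluable per arm. The case for change does not depend on those figures. It rests on the conflict between sections XII.5, V.5 and XII.1, and on the fact that leftover investigational drug is already recovered.

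**What to change.** - Delete the closing sentence of section XII.5.
- Enter in the CRF, per patient and visit, the units of No. 1 and No. 2 medication dispensed and returned, together with the dose prescribed for that interval, and derive the percentage of the prescribed amount taken.
- Define compliance for analysis without using glucose.
- State that this measure, with diary information, is how item 5.2 and per-protocol membership are ascertained. The item 5.2 threshold itself is not questioned here.
- Record metformin use by a diary or CRF entry, since the schedule provides no metformin returns.
- Report compliance by arm, and flag low takers in the response and failure phenotypes for goals 2.1 and 2.4.
- Add one adherence-based sensitivity analysis of the primary endpoint, labelled as supportive because it conditions on post-randomization behaviour.

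The cost is a few CRF fields, one table and one supportive analysis. Return counts can overstate intake, because drug not returned is not necessarily drug taken, but they do not depend on the glucose result.
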